## Methods

### Study setting

The study is performed in the EMS of the city of Wiesbaden and Rhein-Taunus-Kreis (Germany). The operational area in Wiesbaden has five commissioned EMS agencies (four charities, one private provider). The EMS in Wiesbaden has 375 paramedics and serves 462 098 inhabitants.

With regard to the training, close cooperation occurs with the neighboring Rheingau-Taunus-Kreis area. In the context of various difficulties and problems, the controlling authority enabled 301 paramedics from both EMS services to attend the PHTLS courses to create uniform structures and principles [28].

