### Interventions

Paramedical personnel are trained in the care of trauma patients, and the worldwide standardized and certified training program “PHTLS” (Pre Hospital Trauma Life Support) is used.

PHTLS provider courses focus on the professional groups involved in EMS (EMT, paramedics, emergency physicians) for the pre-hospital care of trauma patients and are currently well established in Germany. Among other participants, the helicopter crews of the DRF German Air Rescue will be trained in PHTLS, as well as the German armed forces, which have established PHTLS courses for mission preparation. Thus, PHTLS courses are merged seamlessly with ATLS courses for clinical care in emergency departments [8].

The central link between the PHTLS and ATLS courses is uniform communication and the priority-based approach [22].

In the two-day courses, the participants obtain a complete procedure for the structured treatment of trauma patients, in addition to trauma-specific skills; the classes conclude with a written and practical exam.

PHTLS courses are characterized by the extensive variety in the teaching methods (lectures, practical case studies), with a close instructor- participant ratio (1:3), many practice activities and continuous interaction.

In addition to various skills, the priority-based structure, ABCDE (Airway, Breathing, Circulation, Disability and Exposure), is taught and practiced in scenario-based training sessions. The “ABCDE” method provides structure for patient treatment and ensures that other therapeutic measures are objectified [15].

The PHTLS manual (2^nd^ German edition), which forms the basis for the German PHTLS courses [35], is sent to the participants before the course and is intended to provide the course content with the following priorities:

▪ Safety for EMS staff and patients

▪ Involvement of the accident kinematics in the assessment

▪ Priority-based treatment-principles, “treat first what kills first”

▪ Rapid and correct c-spine immobilization

▪ Immediate repair of airway (A) problems

▪ Evaluation of the ventilation, rapid oxygen administration and treatment of tension pneumothorax

▪ Stop external bleeding and minimization of internal bleeding, e.g. with the pelvic sling

▪ Positioning of axis fractures, and immobilization of the patient if necessary

▪ Treatment of hypothermia

▪ Insertion of iv-lines and fluid resuscitation

▪ Neurological assessment with GCS (Glasgow Coma Scale) and pupil status

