#### Video recording

In the 14 planned courses, 4 video recordings of scenarios completed by three-person teams will be made at t0. A total of 56 teams (168 participants) will be recorded. At t1, video recordings will be made. At this point, three records will be possible, and 12 teams per course will be filmed. In 14 courses, we expected up to 168 teams. The recordings will be made with four camcorders (Panasonic HD Camcorder HC-V100) and recorded on SD Memory Cards.

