### Data management

The data collection, coding, routing and analysis are coordinated with the data protection officer of the University of Tuebingen and the University of Tuebingen Hospital. The participants will be informed about the study prior to the course, and their questions about it will be answered.

The declarations of consent from the participants for the video analysis are available; the consent declarations assure permission for the recording, analysis and storage of the study data. The number of participants will be registered as a negative figure.

For the questionnaires and time contact, t2 is a declaration of consent for the available participants. This declaration is separated from the questionnaires on site. The questionnaires are pseudonymized with a four-digit code to represent the relationship between the different times, not to establish a connection to the participants.

The analysis of the defined characteristics in the EMS-operation protocols is unrelated to the patient data (including the last name, first name and date of birth). Hessian EMS law § 17 permits the use of evaluation data in the context of quality assurance.

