### Statistical methods

The statistical analysis of the end points of the video is based on the assessment tool. The achievable sum scores from the assessment tool are combined with the respective measuring points and, depending on the scale levels, as the mean or median and compared as the independent samples. The statistical tests are dependent on the scale level, and the results are given with the confidence intervals.

The statistical analysis of the questionnaires used the three time points t0, t1 and t2. The individual questionnaires at the respective time points are recorded using Microsoft Excel® 2010 (Redmond, USA). The data are matched in IBM SPSS Statistics 21 software (Illinois, USA) with the pseudonymous ID codes. The data are normally distributed and considered to be metric; the statistical calculation was performed using Student’s t-test for the unpaired two-sided sampling. The significance level is set at α = 0.05.

The evaluations of the EMS protocols in terms of three items, allergies, medication, and the patient’s medical history are conducted by counting the frequency before and after the comparison. The significance level is set at α = 0.1.

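### The questionnaire t-test is unpaired although answers are matched by person, and it ignores the course groups, so the stated 0.05 level may be missed in either direction

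*Protocol article*

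**What the plan says.** Statistical methods sets out the questionnaire analysis in three steps. It covers all measurement times: "The statistical analysis of the questionnaires used the three time points t0, t1 and t2". The forms are linked by person: "The data are matched in IBM SPSS Statistics 21 software (Illinois, USA) with the pseudonymous ID codes". The test is then named: "the statistical calculation was performed using Student’s t-test for the unpaired two-sided sampling". The level follows: "The significance level is set at α = 0.05". No course term is mentioned.

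Data management confirms what the link is for: "The questionnaires are pseudonymized with a four-digit code to represent the relationship between the different times". The Timeline section has the same participants answering just before their course, at its end and one year later. Under Number of participants, a complete return is expected at t0 and t1.

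Training is delivered in groups. The video section reads "In the 14 planned courses, 4 video recordings of scenarios completed by three-person teams will be made at t0". Study setting says that "the controlling authority enabled 301 paramedics from both EMS services to attend the PHTLS courses". Interventions describes two-day courses "with a close instructor- participant ratio (1:3), many practice activities and continuous interaction".

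**The concern.** An unpaired t-test assumes that the t0 and t1 answers come from different, independent people. Here they come from the same people, and the protocol takes care to match them. The test then discards the match.

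The test also treats people within a time point as independent of each other. Participants in one course share teaching and scenarios, so their gains may resemble each other. The Bias section gives two reasons to expect gains to differ by course. Colleagues pass on knowledge as the series of courses proceeds, which could raise the starting level of later courses. Instructors may also set up or weight scenarios differently.

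The trial has a single arm, so the hypothesis on subjective safety rests on this before-after comparison. If the error term is too large, real change may be missed. If it is too small, the p-value overstates the evidence.

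**Working it through.** **Inputs from the protocol.** Unpaired two-sided t-test, level 0.05; the same people at each time, linked by code; 14 courses; 301 people enabled to attend; 168 people filmed at t0.

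**Assumptions.** The protocol gives no within-person correlation r, no course ICC of the change, no standard deviation and no questionnaire sample size. Course size m is taken as 168/14 = 12 to 301/14 = 21.5. This assumes that the 14 courses named under video recording are also the courses of the questionnaire participants.

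**Formulas.** Let n be the number of people and s the standard deviation at each time.

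- Variance the unpaired test uses: 2s²/n
- True variance of the mean change: 2s²(1 − r)·DE/n, with DE = 1 + (m − 1)·ICC
- Actual level ≈ 2·[1 − Φ(1.96/√((1 − r)·DE))]

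The ICC is that of the individual change. A course effect that is the same at t0 and t1 drops out of the difference.

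**Stated level reproduced.** With r = 0 and ICC = 0 the formula returns 0.05. Simulation of fully independent data (14 courses, 4,000 runs) gives 0.048 with 12 per course and 0.051 with 21.

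**Pairing ignored, no course variation in the change.**

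- r = 0.3: √0.7 = 0.837, 1.96/0.837 = 2.34, level 0.019
- r = 0.5: √0.5 = 0.707, 1.96/0.707 = 2.77, level 0.006
- r = 0.7: level 0.0003

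**Both features present.** Design effects are 1 + 11 × 0.05 = 1.55 and 1 + 20.5 × 0.05 = 2.03 at ICC 0.05, and 2.10 and 3.05 at ICC 0.10. Actual level of the stated test:

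| r | ICC 0.05, m = 12 | ICC 0.05, m = 21.5 | ICC 0.10, m = 12 | ICC 0.10, m = 21.5 |
|---|---|---|---|---|
| 0.3 | 0.060 | 0.100 | 0.106 | 0.180 |
| 0.5 | 0.026 | 0.051 | 0.056 | 0.113 |
| 0.7 | 0.004 | 0.012 | 0.014 | 0.041 |

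**Where the two errors cancel.** Setting (1 − r)·DE = 1 gives ICC = r/[(1 − r)(m − 1)].

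- r = 0.3: 0.039 (m = 12), 0.021 (m = 21.5)
- r = 0.5: 0.091, 0.049
- r = 0.7: 0.212, 0.114

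The stated test is too liberal only above these values.

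**If only the pairing is repaired.** The factor (1 − r) disappears and the level becomes 2·[1 − Φ(1.96/√DE)]. At ICC 0.05 this is 0.115 (m = 12) and 0.168 (m = 21.5).

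**Simulation check** (14 courses of 12 or 21, 4,000 runs per setting).

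- Course effect common to t0 and t1 (5–10% of variance), none on the change: the unpaired test rejects 0.034–0.046 without a person effect and 0.004–0.007 with r = 0.5. There is no inflation.
- ICC 0.10, r = 0.5: the unpaired test rejects 0.057 (m = 12) and 0.115 (m = 21); a person-level paired test rejects 0.165 and 0.262.
- A t-test on the 14 course-mean changes stays at 0.041–0.054 in every setting.

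The comparisons assume complete pairs, as the protocol expects for t0 and t1. At t2 some forms may be missing, so the unpaired test would compare partly overlapping groups and the figures would shift.

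**The case against.** A reader might infer that course clustering inflates the stated test, so that its true level is 0.07, 0.17 or 0.26 at ICCs of 0.01, 0.05 and 0.10. The documents do not support that. Those rates, for 21.5 people per course, belong to a person-level paired test, which the protocol does not plan. For the unpaired test as written, lost pairing works against clustering and may dominate. At ICC 0.05, r = 0.5 and 21.5 per course the two nearly cancel. Nor does the usual design effect apply to levels of the score, because every course contributes to both sides of the comparison.

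Other points on that side also have weight:

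- **The ICC of the change is unknown.** PHTLS is described as standardised and certified, with one manual for all, which may keep it small. This stands. The Bias section makes some variation plausible but does not size it.
- **Course size is uncertain.** The 14 courses appear only under video recording, attendance by all 301 is not assured, and study participation is voluntary. This stands, which is why 12 and 21.5 are both shown.
- **The target of inference matters.** If the aim is only the average change across these particular courses, differences between courses need not enter the error term. This is a fair position, but the hypotheses speak of the effect of introducing PHTLS without that limit. Under either target the unpaired test is wrong.
- **A condensed article may leave model details to a fuller plan.** That would excuse silence on a course term. It does not excuse a named test that contradicts the matching described in the same paragraph.

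**Conclusion.** The point holds in this form: the protocol fixes an unpaired test for person-matched data and allows nothing for course groups, so its error term is wrong. The mismatch with pairing follows from the protocol itself. The role of course depends on variation in the change, which is plausible but not quantified there.

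The size and direction of the error cannot be fixed from the document. Across r of 0.3 to 0.7, ICC of the change from 0 to 0.10 and 12 to 21.5 people per course, the actual level runs from 0.0003 to 0.180 against a stated 0.05. All three ranges are assumptions. It would be wrong to conclude that the planned test is known to be too liberal, or that course clustering alone makes it miss its level. It is equally wrong to stop at a paired test if the change may differ by course.

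**What to change.** Replace the sentence naming the unpaired t-test with wording such as: *The change of each matched participant (t1 − t0 and t2 − t0) is analysed in a linear mixed model with a random intercept for course and small-sample degrees of freedom (Satterthwaite or Kenward-Roger). As a simple alternative, the 14 course-mean changes are tested with a one-sample t-test on 13 degrees of freedom.* The two are only approximately equivalent when course sizes differ or t2 forms are missing, so one should be named as the main analysis.

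Record the course number beside the questionnaire code at t0 and t1. Forms are handed out and collected during the courses, so this is practicable. The t2 forms, which come by web or e-mail, can then be assigned to a course through the code.

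The cost is one rewritten sentence and one extra column in the data file, to be cleared with the data protection officer who already oversees the coding. Intervals may be wider than those of a person-level paired test.

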### Research ethics approval

The Ethics Committee of the Medical Faculty of the Eberhard Karls University of Tuebingen and the University Hospital approved the study proposal, number 197/2013BO2, on May 24 2013. The study is registered in the German Clinical Trials Register with the ID DRKS00004713.

### Trials status

The video recordings as well as the basics of the program and the development of the assessment tools are in process (Figure 2).

**Figure 2 F2:**
[figure not shown]
Flowchart of the study, with detailed issues and tasks.

## Discussion

The aim to evaluate the effect of the training or the effect of the program on the patient outcome is understandable, complex and difficult. This study attempts to evaluate the effect of the training on the participants’ behavior.

This is a single-center study and based on scenarios of the treatment given to patients by paramedics. There is interest in developing a multi-center assessment tool. Concrete efforts will be made after the completion of this study to apply the tool for evaluation of emergency physician-based teams including air rescue personnel.

We are aware that the video analysis is influenced by a variety of factors. In addition, the result of the scenario-based patient care is not to transfer 1:1 to the real patient care. To increase the comparability and consistency, a member of the research group will supervise the recordings or even leads them through. Time t0 records are parallel, and the scenarios are directed by leading instructors briefed on the key points and identical criteria to apply to all the cases. An identical situation occurs with t1, with the difference being that in t1, the cases are sequential instead of parallel.

Initially it was planned to visualize the individual measures on a timeline. However, the flow in the scenario is disturbed by the information from the instructors, for example vital signs or by questions from the participants, so it does not seem sensible to use the real-time analysis. In addition, a range of skills such as laying intravascular access or prepare infusions are not real performed.

The results of the questionnaire for the subjective assessment of the participants should be available without special bias, especially we expect a very high response rate. The evaluation of the EMS-protocols focuses on three items, which are trained in the course. But since the SAMPLE scheme is widely used, it remains to be seen how the degree of compliance prior to the course and a possible change is measurable.

This study is being extended to encompass a retrospective analysis of the emergency department data because the participants report a significant change in the care of trauma patients in actual field operations. A question remains concerning the degree to which the training of paramedics in PHTLS has an effect on the treatment of trauma patients by emergency physician-supported teams. Key points will be pre-hospital on-scene time, measures and treatment, and any changes in the patient collective. This part is not completed.

## Abbreviations

ASB: Arbeiter-Samariter-Bund, German aid and welfare organization, EMS agency; ATLS: Advanced trauma life support; DRF: Deutsche Rettungsflugwacht, German Air Rescue; DRK: Deutsches Rotes Kreuz, German Red Cross, a non-profit organization, EMS agency; EMS: Emergency Medical Service; EMT: Emergency medical technician; JUH: Johanniter Unfallhilfe, German Aid and Welfare Organization, EMS agency; MHD: Malteser Hilfsdienst, German Aid and Welfare Organization, EMS agency; PHTLS: Pre-Hospital trauma life support.
